### Community Advisory Board (CAB)

Building upon strong existing partnerships between members of the study team and epilepsy/neurological care partners across the states of Iowa and Ohio, the study team will obtain input from relevant community stakeholders to develop an a priori recruitment and retention strategy intended to maximize enrollment of typically hard-to-reach individuals with epilepsy from underserved and rural communities. The CAB will be composed of up to 16 individuals, including individuals with epilepsy, epilepsy specialists, clinicians, and administrators who practice in rural or underserved communities, and representatives from the Epilepsy Association/Epilepsy Foundation.

There will be 3 video-conference calls prior to the RCT. In the first call, CAB members will review the SMART curriculum and identify potential barriers to recruitment and retention. In the second meeting, CAB members will review the list of barriers and suggest solutions and strategies for reaching people with epilepsy who may not be initially help-seeking and discuss potential methods of retaining these individuals in the program once they are recruited. In the third CAB meeting, the list of strategies will be finalized, and the investigators will obtain input on how these strategies might be best operationalized.

### Phase 2

Phase 2 is a prospective 6-month comparative trial of SMART vs. WL in 160 individuals with epilepsy and a recent NHE. Participants will be randomly assigned (1:1 basis) to receive either SMART (*N* = 80) or WL (*N* = 80) using a computer-generated random number generator created in REDCap during the enrollment process. This is a simple randomization scheme together with permuted block randomization to insure similar treatment and waitlist group sizes. This randomization scheme is unavailable to study staff who enroll participants and assign to treatment or waitlist groups. The participants and nurse and peer educators are not blinded, due to the nature of the intervention. However, the data analysts have no interaction with participants or the nurse or peer educators. The investigators will conduct 8–10 separate and sequential SMART groups with up to 10 individuals in each group. SMART will consist of two main components: a 12-week remotely accessed “intensive” group format stage and a 12-week remotely accessed Web/telephone follow-up stage.

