### Outcomes and analysis

Table 2 outlines study procedures. In addition to demographic and clinical information (age, gender, ethnicity, self-reported cumulative medical illness [19, 20]), health literacy will be assessed [21] to detect persons with limited or marginal health literacy. For both the SMART and the WL groups, research assessments will be done at screening (to establish study eligibility), at baseline, and at 13 weeks, 6 months, 12 months, and 18 months after randomization. Members of the waitlist will also be assessed 13 weeks after starting the SMART intervention. All assessments are suitable for remote administration either by phone or using REDCap (Research Electronic Data Capture), a secure Web application for building and managing online surveys and databases [22]. REDCap will be used for secure data entry and storage.

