#### Primary outcome

The primary outcome will be the proportion of individuals with reduction in their total number of NHEs in the prior 6 months at baseline compared to week 24 of the trial. The prior SMART study had a nonstandard distribution of NHEs and a high proportion of subjects with no NHEs at 6-month follow-up, so a longitudinal binary mixed model (no NHE or at least one NHE) will be used as opposed to a count regression model [10]. The second primary outcome will be the change in NHE counts in the 6 months prior to baseline compared to week 24 of the trial. NHEs are defined as seizures, emergency department visits, hospitalizations, and self-harm attempts. NHE reporting will be via self-report with corroboration by EHR documentation and report of family/support system informants whenever possible. In addition to total NHEs, we will assess NHEs in each category, including seizure frequency and length of stay in days for hospitalization NHEs. These domains (total number of NHEs, seizure frequency, length of hospital stay) will be assessed for differences between the two groups looking at mean and median values. A type I error rate of 0.05 will be considered significant.

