### Data analysis

Descriptive analyses will compare the individuals assigned to SMART or WL using Student’s *T*-test, Fisher’s exact test, and non-parametric tests when appropriate. The primary outcome is whether there is a difference in the proportion of individuals with reductions in the total number of NHEs in the prior 6 months, at baseline, and at follow-up (6 months after randomization) between SMART and WL, compared using a Fisher’s exact test. We will also test for the difference in NHE counts between baseline and follow-up using a non-parametric Wilcoxon-Mann-Whitney test (the distribution of this measure is expected to be non-normal based on our prior experience). Exploratory longitudinal mixed models with a subject-level random effect will be conducted to investigate a binary variable of no NHEs versus at least one NHE and for a count measure of total NHEs from baseline to 10 and 24 weeks. Explanatory variables will include study site, age, gender, race/ethnicity, number of seizure medications, rural/urban continuum status, and attendance or deviations from the study protocol. Analysis will be performed for the intention-to-treat population (all participants enrolled to receive the SMART trial), for the safety population (all participants who received any portion of the SMART intervention), and for the per-protocol population (all participants who completed the SMART intervention). There will be a delay between randomization and baseline assessments for individuals enrolled for both the SMART trial and the waitlist, which may vary based on the recruitment time required for cohorts and the number of cohorts that can be accommodated at one time. Every effort will be made to insure steady recruitment and sufficient numbers of cohorts to accommodate those recruited. In addition, the specific cohorts will be able to be identified for analysis, and if we find marked variability between the cohorts or the delay in starting the intervention, this will be addressed by the data monitoring committee.

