The 12-month and 18-month measurements of NHEs will be compared to baseline and 6-month measurements as well. We will also examine change-over-time in the secondary outcomes using parametric and/or non-parametric tests as deemed appropriate for each measure. NHE measurements will reflect the preceding 6-month time period, except for the 13-week time period. The 13-week NHE measurement will reflect the time period following baseline (when individuals participating in SMART will be having their “intensive” group sessions), and it will be used to assess for within-subject differences from baseline to 13-week and 13-week to 6-month time periods. Note that the 13-week to 6-month NHE count will be derived by subtracting the measurement taken at 13 weeks from the one taken at 6 months. This will allow for a greater understanding of the time course for when the expected reductions occur in the SMART group, which we expect to mostly occur after the “intensive” 8 group sessions have ended. A secondary analysis of NHEs will include a comparison of hospital and emergency department visits. A 2-sided type I error rate of 5% will be considered significant.

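### The self-reported baseline NHE count behind both primary outcomes is taken after open-label randomization and an uncapped delay, and the article gives conflicting time origins for follow-up

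*Protocol article*

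**What the plan says.** The Data analysis section states: "There will be a delay between randomization and baseline assessments for individuals enrolled for both the SMART trial and the waitlist". It describes this delay as one "which may vary based on the recruitment time required for cohorts and the number of cohorts that can be accommodated at one time" and gives no typical or maximum length. Under Phase 2, assignment is generated in REDCap during enrolment, and "The participants and nurse and peer educators are not blinded".

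The Primary outcome section builds both primary outcomes on the baseline count. The first is the proportion of people whose NHE total falls, taken "in the prior 6 months at baseline compared to week 24 of the trial". The second is the change in counts between the same two points. NHEs are self-reported, with corroboration from health records and informants where possible.

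The time origin differs from place to place:
- The Outcomes and analysis section schedules assessments "at baseline, and at 13 weeks, 6 months, 12 months, and 18 months after randomization".
- The Data analysis section makes the primary comparison "at follow-up (6 months after randomization) between SMART and WL".
- The same section says "NHE measurements will reflect the preceding 6-month time period, except for the 13-week time period".
- It then says "The 13-week NHE measurement will reflect the time period following baseline", and obtains the later-period count by subtracting the 13-week count from the 6-month count.
- The week-24 wording under Primary outcome has no stated origin.

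**The concern.** A baseline value in a change endpoint should be fixed before anyone can know the allocation. Here it is recalled and reported by unblinded participants at some point after randomization. If people who know they will start SMART report past events differently from people who know they will wait, the difference passes directly into the change score. If people in one arm leave before the baseline assessment, they have no change score at all, and the arms compared are no longer those randomized.

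The timing is a separate problem. With baseline later than randomization, a 6-month look-back that starts at randomization includes the waiting period, and so does the look-back at baseline. Events in that period cancel in the change score, and the SMART arm has less than 6 months of post-baseline time. Depending on which section is followed, two analysts could compute different primary outcomes from the same participants.

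**Working it through.** **Notation.** Randomization is week 0, baseline is week d, and 6 months is 26 weeks. The article gives no value for d, so 4 and 8 weeks are assumptions.

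**Windows under the two anchors**

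| Follow-up timed from | Baseline window | Follow-up window | Weeks in both | Post-baseline weeks |
|---|---|---|---|---|
| Randomization | d−26 to d | 0 to 26 | d | 26−d |
| Baseline | d−26 to d | d to d+26 | 0 | 26 |

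**Dilution under the randomization anchor.** Let the weekly rate be λ, halved in SMART from baseline onward. The expected baseline count is 26λ. The expected SMART follow-up count is dλ + 0.5(26−d)λ. The expected measured reduction is therefore 0.5 × (26−d)/26.
- d = 4: shared weeks 4/26 = 15.4%; measured reduction 0.5 × 22/26 = 42.3%.
- d = 8: shared weeks 8/26 = 30.8%; measured reduction 0.5 × 18/26 = 34.6%.

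This assumes the full effect starts at baseline. The Data analysis section expects most of it after the group sessions. The weeks lost are the last d of the post-baseline period, so the dilution could be larger. SMART lasts 12 + 12 = 24 weeks. If sessions start at baseline, any d above 2 weeks puts the 6-month assessment before the program ends.

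**The 13-week subtraction.** With visits timed from randomization, the 13-week count covers weeks d to 13 and the 6-month count covers weeks 0 to 26. Their difference covers weeks 0 to d plus weeks 13 to 26, which is 13 + d weeks: 17 weeks at d = 4 and 21 at d = 8. With baseline as time zero the difference covers exactly the later 13 weeks. The subtraction therefore works only under the baseline anchor, which contradicts the other two statements.

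**Week 24 against 6 months.** 26 × 7 − 24 × 7 = 182 − 168 = 14 days. A 6-month look-back taken literally at week 24 reaches 2 weeks before its origin under either anchor. This is minor, but the same definition should settle it.

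**Stated power.** 160 × 0.80 = 128 reproduces. The 86% and 89% cannot be reproduced, because the article gives no per-arm proportions and no Laplace shift or scale. The loss of power can therefore only be illustrated. Gamma-Poisson models with 64 per arm and the rate halved gave these Fisher powers under the randomization anchor:

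| Assumed 6-month mean, shape | No delay | 1 month | 2 months | 3 months |
|---|---|---|---|---|
| 6, 1 | 87% | 82% | 70% | 61% |
| 12, 0.7 | 96% | 94% | 90% | 81% |

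A third setting (mean 10, shape 0.5, with the eligibility rule applied) lost only about 2 to 3 points at 8 weeks, from 98–99% to 96%. The loss depends heavily on event rates that the documents do not give.

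**Differential reporting.** This is also illustrative. With no true effect, mean 6 and shape 1, suppose the SMART arm alone over-reports its baseline count by 10%, 20% or 30%. The Fisher false-positive rate rises from about 3% to 8%, 21% or 40%. Nothing in the documents says such a difference will occur. The opposite pattern would hide a benefit.

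**The case against.** The strongest counter-argument concerns the overlap. A reader might infer that the two 6-month windows do overlap and that power falls below the stated 86% and 89% by a known amount. The documents do not support that. The 13-week definition and the subtraction imply that baseline is time zero. On that anchor the overlap is zero for any delay, apart from the small week-24 discrepancy. What the text establishes is a conflict of origins. The simulated powers rest on assumed rates and are not calibrated to the plan.

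A reader might also infer that participants know their arm when they give the baseline count. The article never says when allocation is disclosed. It says only that participants are unblinded because of the nature of the intervention. Exposure to bias is a fair conclusion, but actual bias is not shown.

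Overlap and bias must also be kept apart. If delays are similar in the two arms, overlap dilutes the contrast and does not manufacture a benefit. Bias needs reporting, dropout or delay to differ by arm.

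The article does offer safeguards: the delay is disclosed and applies to both arms, steady recruitment is promised, cohorts can be identified for analysis, marked variability goes to the data monitoring committee, and NHEs are corroborated where possible. These are partial. The committee referral is triggered only after the fact and cannot recreate a baseline taken before allocation. Corroboration is not assured for every participant.

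**Conclusion.** The concern holds in two parts. First, the baseline count for both primary outcomes is self-reported after open-label randomization and a variable, uncapped delay, with no statement that allocation is withheld until then. The risk of differential reporting and pre-baseline dropout is real, but its size and direction are unknown. This part holds whichever anchor is meant.

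Second, the time origins contradict one another and must be reconciled. The consequence is conditional. Under the randomization anchor, d weeks enter both counts, 26−d weeks of post-baseline follow-up remain, and a true 50% reduction is expected to be measured as 42% at 4 weeks or 35% at 8. These figures assume those delays, a constant rate and an immediate effect. Under the baseline anchor this dilution does not arise. No specific loss of power can be claimed.

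**What to change.** Complete the baseline NHE count before allocation is generated or revealed, and where possible randomize when a cohort is ready to start. Define one time zero for both arms. The baseline window is the 6 months ending at it, and the follow-up window is the 6 months starting at it. Use that definition in the Outcomes and analysis section, the Primary outcome section and throughout Data analysis, including the 13-week count, and state week 24 or 26 weeks consistently.

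If randomization must stay early, record a 6-month NHE count at the pre-randomization screening and use it as baseline, with follow-up starting at one time zero defined identically in both arms. The text says only that screening establishes eligibility, and the schedule table is not shown, so this count may have to be added to that contact.

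The cost is some extra scheduling: consented participants wait before rather than after allocation, and enough of them must be held unallocated to fill a group and its waitlist counterpart. The change should be made before randomization starts, because a pre-allocation count that was never taken cannot be recovered later.

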### Experimental intervention

The SMART curriculum is divided into 2 steps. Step 1 consists of eight group format 45–60-min sessions with up to 10 participants per group, which will be collaboratively delivered by a nurse educator and a peer educator. The intervention will be delivered in a Web-based format emphasizing interactive discussion with a secure videoconferencing system. Participants will be able to log on and interact via audio and/or video. Telephone call-in will be available for those who do not have Internet access. Patients will receive e-mail and phone call reminders of sessions, and make-up sessions will be available. The initial group-session portion of SMART will be completed over 10–12 weeks (Table 1). Following the step 1 group sessions, step 2 consists of 3 brief (no more than 15 min) monthly Web-based or telephone maintenance sessions conducted by the nurse educator. Telephone sessions will address ongoing issues of epilepsy self-management including treatment adherence. Additionally, the nurse will serve as a facilitator of linkage between the individual’s epilepsy care clinicians by providing SMART program status updates to providers.

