### Waitlist (WL) control

Individuals randomized to WL will continue in their usual care. After they complete their 13-week and 6-month assessments, which are identical to the SMART group assessments, WL individuals will begin participating in the SMART intervention for the next 12 weeks. Once the WL individuals begin participating in SMART, they will have research assessments at 13 weeks, 6 months, and 12 months after beginning SMART.

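### The week 13 to 6-month NHE count, which covers the period when SMART is expected to work, is assigned only to within-subject comparisons although an untreated randomized control is available for it

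*Protocol article*

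**What the plan says.** The Data analysis section of the protocol article predicts the timing of the effect: reductions "which we expect to mostly occur after the “intensive” 8 group sessions have ended". Under Experimental intervention, "The initial group-session portion of SMART will be completed over 10–12 weeks".

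Both primary outcomes use the whole follow-up window. The first is this: "proportion of individuals with reduction in their total number of NHEs in the prior 6 months at baseline compared to week 24 of the trial". For the other, "The second primary outcome will be the change in NHE counts in the 6 months prior to baseline compared to week 24 of the trial". Data analysis adds that "NHE measurements will reflect the preceding 6-month time period, except for the 13-week time period", so the week-24 count includes the session weeks.

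The same section obtains a week 13 to 6-month count by subtracting the 13-week count from the 6-month count. Of the 13-week measurement it says that "it will be used to assess for within-subject differences from baseline to 13-week and 13-week to 6-month time periods", and that this will "allow for a greater understanding of the time course for when the expected reductions occur in the SMART group".

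The Waitlist (WL) control section says when controls start SMART: "After they complete their 13-week and 6-month assessments, which are identical to the SMART group assessments". Controls are therefore measured on the same schedule and are untreated up to month 6.

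**The concern.** The plan makes a prediction about timing, builds the variable that could test it, and then names an analysis that does not use the control arm. Every participant enters because of an NHE in the last 6 months, so counts can fall after baseline without treatment. The two follow-up periods may also differ in length, and plain subtraction does not allow for that. Both artefacts point the way the plan predicts: fewer events later.

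At stake is whether the time-course finding can be attributed to SMART. The waitlist begins SMART after its 6-month assessment, so the 12- and 18-month visits cannot provide the missing comparison.

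**Working it through.** **1. The plan's own figures.** From Sample size calculations: 160 randomized with 20% attrition gives 160 × 0.80 = 128, or 64 per arm. This reproduces. The stated powers (86% Fisher, 89% Wilcoxon-Mann-Whitney) cannot be reproduced, because neither the two proportions nor the Laplace shift and scale are given. Solving backwards at 64 per arm, 86% Fisher power needs a difference of about 23.5 to 28 percentage points for waitlist proportions of 20% to 65%. For 89% Wilcoxon power the shift is about 0.68 Laplace scale units. These are effects on the full 6-month window.

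**2. Window lengths.** If follow-up is read at week 24, the early period is 13 weeks and the late period 24 − 13 = 11 weeks. At a constant event rate the raw late count is 11/13 = 0.846 of the early count, a 15% fall with no effect at all. If 6 months means 26 weeks, the periods are 13 and 13 and this artefact disappears. The article uses both week 24 and 6 months.

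**3. What the within-subject contrast shows under no effect.** Assumptions, none of them from the article: 64 participants; gamma-Poisson counts with mean 4, 8 or 15 NHEs per 6 months before selection; at least one NHE at baseline; constant individual rates; 13- and 11-week windows. A signed-rank test of raw late against raw early counts was significant in 28%, 47% and 73% of trials respectively. A separate run gave about 25% to 66%. The between-arm test of the late period was significant in about 4%. Scaling counts to rates, or using a 26-week endpoint, removes the inflation, so in this model all of it comes from window length.

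**4. Regression to the mean.** This mainly affects contrasts with baseline. With constant individual rates it is small. For mean m = 4 and gamma shape k = 0.7:
- Probability of no baseline event: (1 + m/k)^(−k) = 6.714^(−0.7) = 0.264.
- Baseline mean among those eligible: 4/(1 − 0.264) = 5.43.
- Expected 6-month follow-up mean: (4 − 0.264 × 0.596)/(1 − 0.264) = 5.22, where 0.596 = k/(k/m + 1) is the expected rate of those with no baseline event.
- Fall: 1 − 5.22/5.43 = about 4%.

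If people enrol during a temporary cluster of events, the fall is larger, and it can continue from the early to the late period. The article gives no figure for this. A within-subject contrast cannot remove it whatever its size; a randomized comparison cancels it in expectation.

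**5. Power of a between-arm late contrast.** Illustration with 64 per arm, mean 5 or 15 NHEs per 6 months, frailty variance 1 or 3, two 12-week halves, and Wilcoxon on change from baseline:

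| Rate ratio early / late | Full-window power | Late-period power |
|---|---|---|
| 1.0 / 0.5 | 46–93% | 84–100% |
| 0.8 / 0.4 | 81–100% | 93–100% |
| 0.6 / 0.6 | 82–100% | 67–99% |

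The late contrast gains when the effect is late, as the plan expects. It loses when the effect is uniform, by under one point to about 15 points across the four settings.

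**The case against.** **The primary outcomes are diluted and the trial is underpowered.** A reader might infer this. If SMART did nothing for 13 weeks and then halved the rate, the 24-week count would fall by only 11/24 × 50% = 23%. The documents do not support the inference. Sample size calculations states power for replicating the earlier trial's difference in 6-month counts, so if that window matched, any slow onset is already in the planned effect. The scenario is also an assumption: the article says mostly late, not wholly late. It does not fit the article's only stated effect either. A 50% reduction over 24 weeks with no early effect would need a late reduction of 50%/(11/24) = 109%, which is impossible. Total events over 6 months is a proper target for a replication.

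**The late effect is never tested against waitlist.** This also goes too far. Data analysis plans exploratory longitudinal NHE models through week 24, and Secondary/additional outcomes compares self-reported seizure frequency between groups at 13 and 24 weeks. Neither is stated to isolate the late-period NHE count. The models' listed variables include no arm or arm-by-time term (the list need not be complete), and they refer to week 10, whereas the assessment schedule has week 13.

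**Within-subject changes could be compared between arms.** True, since the second primary outcome is exactly that. But the article does not say so for the 13-week split, and it states the purpose in terms of the SMART group.

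**This belongs in the analysis plan.** Arm-by-time terms often do. Here, however, the article names a specific method, and it is the weaker one.

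**The late count is fragile.** This stands. It subtracts two mainly self-reported counts with different recall periods. Data analysis times follow-up from randomization but describes a variable delay before baseline, so the two counts may not start together.

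**Conclusion.** The concern holds in a limited form. The article predicts a late effect, derives the late count, and names only an uncontrolled use for it, although an untreated randomized control exists for that period and for no later post-session period. Under no effect, a raw within-subject early-versus-late contrast could appear significant in roughly 25% to 73% of trials. That range rests on assumed event rates, on 13- and 11-week windows and on unscaled counts; rate-scaling or a 26-week endpoint would bring it back to nominal. Regression to the mean would remain, of unknown size.

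The primary outcomes are unaffected. They are legitimate, and nothing here shows power below the stated 86% and 89%. The weakness is in the attribution of the time course, and it is inexpensive to repair.

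**What to change.** Keep both 6-month primary outcomes. In Data analysis, replace or supplement the within-subject time-course analysis with one prespecified secondary comparison of SMART and waitlist in all randomized participants. It can be either of these:
- the week 13 to 6-month NHE count, adjusted for baseline NHE count; or
- an arm-by-period contrast (weeks 0–13 against week 13 to 6 months), with an offset for window length.

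State its role among the secondary outcomes. State also that the 13-week and 6-month counts start at the same time point, and reconcile this with the delay between randomization and baseline; otherwise the subtraction does not give the intended period.

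The cost is a change of wording and one more secondary test. No new visits or data are needed. The subtracted self-report count is noisier than the 6-month total and less powerful than the full window in most uniform-effect scenarios, which is a further reason to leave the primaries as they are.

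### The 13-week NHE count covers half the window of the baseline count with no rate scaling stated, so a raw within-subject comparison falls by about 50% with no true change

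*Protocol article*

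**What the plan says.** All of this is in the protocol article.

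- **Windows.** Under Data analysis, "NHE measurements will reflect the preceding 6-month time period, except for the 13-week time period". For the exception, "The 13-week NHE measurement will reflect the time period following baseline".
- **Use of the 13-week count.** The same paragraph says "it will be used to assess for within-subject differences from baseline to 13-week and 13-week to 6-month time periods".
- **Late period.** "13-week to 6-month NHE count will be derived by subtracting the measurement taken at 13 weeks from the one taken at 6 months". The aim is to see when reductions happen, "which we expect to mostly occur after the “intensive” 8 group sessions have ended".
- **Exploratory models.** Mixed models with a subject-level random effect are planned for a binary measure (no NHE versus at least one) and "for a count measure of total NHEs from baseline to 10 and 24 weeks". No exposure term or rate scaling is mentioned.
- **Visit clock.** Outcomes and analysis schedules assessments "at 13 weeks, 6 months, 12 months, and 18 months after randomization", while Data analysis says baseline assessment may follow randomization by a variable delay.
- **Primary tests.** Data analysis compares the 6 months before baseline with 6 months after randomization, by Fisher's exact test (proportion with a reduction) and a Wilcoxon-Mann-Whitney test (change in count).

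**The concern.** A count grows with the time over which it is taken. Baseline covers about 26 weeks and the 13-week measure about 13, so their raw difference is negative for a participant whose event rate has not moved. The any-NHE indicator behaves the same way: less time means less chance of an event. The mixed models would inherit this if fed these counts, and the 24-week count would also contain the events already counted at the early visit.

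At stake is the within-subject time course. A fall of about half from window length alone is close in size to the reduction of more than 50% that the Sample size section cites from the original efficacy trial, so within an arm the artefact could not be told from success. The derived late count adds a second weakness, since it is the difference of two self-reports made at different times over overlapping periods. The models also name a 10-week time point, which neither the assessment schedule nor the rest of Data analysis has.

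**Working it through.** The plan gives no figure for the 13-week analysis, so there is none to reproduce.

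**Inputs from the document.** Baseline window 6 months, taken as 26 weeks; early window 13 weeks from baseline; end of follow-up given as 6 months or as week 24; 128 participants expected at 6 months, or 64 per arm; two-sided 5% level.

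**Inputs assumed.** A constant event rate with no treatment effect. For the simulation: gamma-Poisson counts with dispersion 0.5 and means of 1 to 20 NHEs per 26 weeks. The document gives neither mean nor dispersion.

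**1. Window length.** Expected count = rate × window, so the spurious fall is 1 − (later window / earlier window).

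- Raw 13-week count against baseline: 1 − 13/26 = 50%.
- If the early window really were 10 weeks: 1 − 10/26 = 62%.
- 0–13 weeks against 13–26 weeks: 1 − 13/13 = 0%.
- 0–13 weeks against 13–24 weeks: 1 − 11/13 = 15%.
- Any of these as rates per week, or with a log-window offset: 0%.

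**2. Any-NHE proportion.** With dispersion k and mean m, P(at least one) = 1 − (k/(k + m))^k. For m = 2 over 26 weeks: 1 − (0.5/2.5)^0.5 = 0.55. Over 13 weeks, m = 1: 1 − (0.5/1.5)^0.5 = 0.42. Simulation gave 0.556 and 0.421.

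**3. Signed-rank test with no true change** (64 participants, 1,000 runs; the first four result columns are rejection rates).

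| Mean per 26 wk | 26 vs 13 wk, raw | 13 vs 13 wk | 13 vs 11 wk | 13 wk vs derived late count, 80% recall | Derived count negative | Any NHE, 26 wk | Any NHE, 13 wk |
|---|---|---|---|---|---|---|---|
| 1 | 85.6% | 4.1% | 8.5% | 9.2% | 3.5% | 0.423 | 0.294 |
| 2 | 98.8% | 4.6% | 11.6% | 14.1% | 4.0% | 0.556 | 0.421 |
| 5 | 100% | 5.7% | 30.1% | 29.7% | 4.0% | 0.698 | 0.590 |
| 10 | 100% | 3.5% | 43.3% | 48.2% | 3.3% | 0.783 | 0.700 |
| 20 | 100% | 5.2% | 71.4% | 74.2% | 2.5% | 0.845 | 0.781 |

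The entry requirement of a recent NHE was not imposed in these runs.

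**4. Subtraction, recall loss.** Let E and L be the true early and late counts, and r the share of early events still reported at 6 months. The derived late count is (rE + L) − E. With equal expected E and L, its mean is r times the true one. For r = 0.90, 0.80 or 0.70 (assumed) it is 10%, 20% or 30% too low.

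**5. Subtraction, delay.** Suppose both visits run from randomization and baseline comes d weeks later (assumed). The early window is then 13 − d weeks. A 26-week look-back minus it leaves 13 + d weeks, of which d precede baseline. For d = 2 this is 11 against 15 (ratio 1.36); for d = 4 it is 9 against 17 (ratio 1.89). This raises the derived late count relative to the early one.

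**The case against.** The strongest reply concerns the key sentence. Both of its phrases can modify the periods, so it may contrast baseline to week 13 with week 13 to month 6. The subtraction that follows creates just such a pair, and the aim of locating reductions relative to the intensive sessions fits. That reading is at least as natural as the other. A reader might infer that a spurious 50% fall is built into the plan; the document does not support that, because it holds only if the 13-week count is set raw against baseline. The reply is not complete, though. A statement about when reductions occur needs a pre-treatment reference, and the only one is the 6-month baseline count.

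Second, the mixed models are labelled exploratory, the text does not say which counts enter them, and an offset is a detail that an analysis plan not shown here may supply. This stands, so the point about the models is conditional. The conflict between 10 and 13 weeks does not depend on it.

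Third, a reader might infer that the subtraction favours the investigators' expectation of a late reduction. Recall loss would, but its size appears nowhere in the document, and the Primary outcome section provides for corroboration from health records and informants where possible. A delay before baseline works the other way. The net direction is unknown.

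Fourth, a reader might infer a threat to the primary result or to the comparison of arms. Neither primary test uses the 13-week count, and the Waitlist control section gives both arms identical assessments, so a window effect is common to both at a given visit. The Primary outcome section also mentions a longitudinal binary model, but Data analysis names the Fisher test for the primary comparison and calls the mixed models exploratory; I follow the latter.

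**Conclusion.** The point holds as one about the within-subject time course and the exploratory models. It should be corrected but does not endanger the primary analysis. The unequal windows are the document's own, and the 50% figure needs only a constant rate and a raw comparison with baseline. Under the two-halves reading the figure is 0% or about 15%, depending on whether follow-up ends at 6 months or at week 24. The rejection rates and any-NHE proportions illustrate the consequence and rest on assumed event rates and dispersion. The bias from subtraction is possible in both directions and cannot be sized from the document. The 10-week time point is a plain inconsistency.

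**What to change.** 1. State which periods are contrasted within subject.
2. Analyse NHE counts as rates in disjoint periods (6 months before baseline, 0–13 weeks, 13 weeks to 6 months), with log days at risk as an offset in the count models.
3. Compare the any-NHE indicator only across windows of equal length.
4. At the 6-month visit, record NHEs since the 13-week assessment separately or by date rather than relying on subtraction. Keep the full 6-month total for the primary outcome. If subtraction is kept, start the 6-month look-back at baseline and say how negative values are handled.
5. In Data analysis, change 10 weeks to 13 and reconcile 24 weeks with 6 months.

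The cost is analysis wording and a little extra data entry at an existing visit. The late-period report and the 6-month total may not add up exactly with the 13-week report and would need reconciling. Item 4 is best settled before 6-month data accrue, because late events that were neither dated nor asked about separately cannot be recovered at analysis.
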